##### Evaluation

For 12 months, routinely reported RiskMan data will be extracted weekly and point-prevalence chart audits will be conducted quarterly on all four wards. On the intervention wards, data will be collected to evaluate the feedback reporting process and to elicit the opinions of managers and nurses with respect to the understandability, usefulness and usability of the report content. The findings will inform modifications to the report for future waves of report delivery.

On a quarterly basis, 1 week following delivery of the feedback report, nurses will be invited to complete the post-feedback survey, a brief, paper-based survey [11]. The researchers, in conjunction with the key stakeholder reference group, will consider the findings of the survey and modify future feedback reports accordingly. These modifications will then be re-evaluated by survey. Thus, a series of feedback reports, each containing the most current medication error report rates (from the point-prevalence medication chart audits) and medication-related errors and AEs (from RiskMan data) will be produced and each will be informed by survey data evaluating the previous reports. If and when the survey data no longer indicate the need for future modifications, the feedback report will not be modified and the staff will not be re-surveyed. Completion of the survey will be voluntary, and return of the survey will imply consent. Survey data will be manually entered into an IBM SPSS Statistics [49] database for analysis. Following the final 2 cycles of feedback, nurses on the intervention wards will be invited to participate in a focus group interview to discuss the process of using the feedback.

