**Methods/design:**

A quasi-experimental design, incorporating two pairs of matched wards at an acute care hospital, is used. Randomisation occurs at the ward level; one ward from each pair is randomised to receive the intervention. A key stakeholder reference group informs the design and delivery of the feedback intervention. Nurses on the intervention wards receive the feedback intervention (feedback of analysed audit data) on a quarterly basis for 12 months. Data for the feedback intervention come from medication documentation point-prevalence audits and weekly reports on routinely collected medication error data. Weekly reports on these data are obtained for the control wards. A controlled interrupted time series analysis is used to evaluate the effect of the feedback intervention. Self-report data are also collected from nurses on all four wards at baseline and at completion of the intervention to elicit their perceptions of the work context. Additionally, following each feedback cycle, nurses on the intervention wards are invited to complete a survey to evaluate the feedback and to establish their intentions to change their reporting behaviour. To assess sustainability of the intervention, at 6 months following completion of the intervention a point-prevalence chart audit is undertaken and a report of routinely collected medication errors for the previous 6 months is obtained. This intervention will have wider application for delivery of feedback to promote behaviour change for other areas of preventable error and adverse events.

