#### Survey data sources

Two other sources of data are surveys of nurse participants:The Alberta Context Tool (ACT) will be administered twice to nurses in all four wards: at baseline, prior to introduction of the feedback reports and 12 months following baseline data collection [45, 46].The post-feedback survey will be administered four times to intervention ward participants (1 week following each feedback report) [11].

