#### Testing the SMART intervention

##### Administration

In conjunction with the key stakeholder reference group, the timing and mechanism for delivery of the feedback report will be determined. At a mutually convenient time, the researcher will meet with the relevant nurse unit managers of the two intervention wards to explain the project and arrange a suitable time for delivery of the feedback reports. A brief information session will be conducted in conjunction with delivery of the first feedback report, at a time and location determined by the nurse unit manager. Feedback reports will be provided on a quarterly basis for 12 months. The “usual care” wards will not receive the SMART intervention.

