##### Process measures

Process measures include self-reported uptake of feedback reports (survey data), intent to change behaviour (survey data) and perceptions of the feedback report (survey data on report content, presentation; interview data).

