### Analysis

Quantitative methods will be used to analyse the survey data. Analysis will involve the use of simple descriptive statistics, including frequencies and cross tabulations, and bivariate analysis using correlations. Interrupted time series analysis will be used to assess for change over time in response to the feedback. Outcomes will include error rates identified during the point-prevalence chart audits and the error report rates identified from RiskMan data. These data will be aggregated at ward level.

We will also examine RiskMan data for the 12-month period prior to the intervention. Intervention dose will be the main predictor, operationalised as the number of nurses on the ward who self-report reading the feedback reports. Aggregated at ward level, scores for the eight dimensions of organisational context will also be included as predictors of medication error reporting rates. Multivariate regression analyses will include cluster correction to adjust for ward and site effect. Content analysis will be used to analyse string variable responses to open-ended questions about suggestions to improve reports. Qualitative data will be analysed using content and thematic analysis techniques.

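### The post-feedback survey is fixed at four rounds in two places but may stop early in another, which could leave reading dose, uptake and intent unmeasured in later feedback cycles

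*Protocol article*

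**What the plan says.** All references are to the protocol article.

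- **Survey data sources** fixes the number of rounds: "The post-feedback survey will be administered four times to intervention ward participants", each one week after a report.
- **Abstract, Methods/design** agrees and sets no condition: "following each feedback cycle, nurses on the intervention wards are invited to complete a survey".
- **Administration** sets the delivery schedule: "Feedback reports will be provided on a quarterly basis for 12 months". Delivery does not depend on survey results.
- **Evaluation** opens with the same schedule: "On a quarterly basis, 1 week following delivery of the feedback report, nurses will be invited to complete the post-feedback survey". It then describes using each round to revise the next report, and ends with a conditional rule. When responses stop pointing to changes, "the feedback report will not be modified and the staff will not be re-surveyed".
- **Analysis** states: "Intervention dose will be the main predictor". It defines dose as the number of nurses on a ward who say they read the reports.
- **Instruments** places the questions on receiving and reviewing the report, and on intent to change, in the post-feedback survey. **Process measures** gives survey data as the source of uptake and of intent.

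**The concern.** The survey does two jobs. It guides revision of the report, and it supplies the declared main predictor and two process measures. The stopping rule in the Evaluation section suits the first job: a report that needs no change needs no further comment on its design. It does not suit the second, because nurses can go on reading, or stop reading, a report that is no longer being revised.

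The rule also conflicts with the fixed count given elsewhere. If the condition is met before the fourth survey, the article instructs both that the remaining rounds be held and that they not be held.

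At stake are reading dose, uptake and intent in the later cycles. Any gap would be tied to earlier survey answers, so it could not simply be treated as random. An analysis plan could say how to handle such a gap, but it could not recover answers that were never asked for. Dose matters to the study's own purpose, since the Background lists the intensity of feedback among the characteristics it hopes to learn about.

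**Working it through.** **1. Reproduce the stated count.** Reports are quarterly for 12 months (Administration), so 12 / 3 = 4 reports. One survey after each gives 4 rounds, which matches the four in Survey data sources.

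**2. Count the rounds that the stopping rule allows.** Let k be the survey at which responses first call for no change. Rounds k+1 to 4 are then not held. No minimum is given, so k may be 1, 2 or 3. If the condition is not met before the fourth survey, all 4 rounds are held (k = 4 below). Reports are still delivered in the 4 − k cycles without a survey.

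**3. Look for another source of the same variables.**

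| Source | Timing | Could it supply a reader count per ward? |
|---|---|---|
| Post-feedback survey | One week after each report | Yes; it asks about receipt and review |
| Alberta Context Tool | Baseline and 12 months | No; it measures work context |
| Focus groups | After the final two cycles | No; qualitative, consenting nurses only |
| Incident reports and chart audits | Weekly and quarterly | No; these are the outcomes |

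No other quantitative source of reading, uptake or intent is described.

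**4. Size if dose is per ward and cycle.** This is an assumption, because the Analysis section does not say. With 2 intervention wards (Administration) there would be 2 × 4 = 8 values. If surveying stops on both wards together, also an assumption, the loss is 2 × (4 − k):

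| Last survey held (k) | Values collected | Values lost | Share lost |
|---|---|---|---|
| 1 | 2 | 6 | 6/8 = 75% |
| 2 | 4 | 4 | 4/8 = 50% |
| 3 | 6 | 2 | 2/8 = 25% |
| 4 | 8 | 0 | 0% |

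**5. Size if dose is cumulative.** Each ward keeps one value, but it covers only the first k reports. Reading of the remaining 4 − k reports (3, 2 or 1 of the 4 for k = 1, 2 or 3) is not counted. Dose then partly reflects how many surveys were held.

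**6. What does not depend on the survey.** The outcomes are the routine incident reports, extracted weekly, and the chart audits, done quarterly, on all four wards. Their collection continues whether or not nurses are surveyed, so the controlled interrupted time series comparison does not need the survey.

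**The case against.** The strongest reply is that the Evaluation sentence is loosely worded and is not a chosen stopping rule. Just before it, the article says that modifications will be evaluated again by survey. Not surveying again could then mean only that an unmodified report needs no such re-evaluation, while the quarterly survey goes on. That reading would agree with the Abstract and Survey data sources. It is possible, but it is not what the sentence literally says, and staff following the text could reasonably stop. The wording needs changing on either reading.

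Three further points stand and limit the concern:

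- **The stop is conditional.** A reader might infer that surveying will stop and that the main predictor is removed. The text supports only that it may stop. Dose already collected is kept, and nothing is lost if changes are still being sought up to the fourth survey. The largest loss requires that no change be wanted after the very first report, and the article gives no basis for judging how likely that is.
- **Eight dose values are not a planned figure.** The Analysis section speaks of reading the reports in the plural and does not say per cycle. The percentages hold only under that assumption.
- **No direction or size of bias is shown.** The trigger is whether changes to the report are wanted, which is not the same as reading it or intending to change. The gap would depend on earlier answers, but what that does to a dose–response estimate cannot be worked out from the article.

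The focus groups cover receiving, reading and using the reports, so later use is not wholly unobserved. They cannot give a reader count.

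**Conclusion.** The sections disagree, and the disagreement can affect the data. Followed literally, the Evaluation section could leave reading dose, uptake and intent to change uncollected in up to three of the four cycles while feedback is still being delivered. Per ward and cycle that is 0 to 6 of 8 values. For a cumulative dose, it is the uncounted reading of up to three reports. Both sizes assume that the stop applies to both intervention wards together and that no other quantitative source of these variables exists beyond those the article describes.

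A reader might go further and infer that the evaluation of the intervention itself is compromised. The article does not support that. The incident-report and chart-audit outcomes are collected on all four wards regardless of the survey, and the controlled ward comparison over time does not use it. What is exposed is the regression on dose and the survey-based process measures. That is still worth correcting, because dose is the named main predictor and unasked questions about reading cannot be reliably reconstructed later.

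**What to change.** Separate the two purposes of the survey. Administer the items on reading, uptake and intent to change after all four reports, whatever earlier rounds showed, and let only the report-improvement items lapse once no changes are sought. Reword the last part of the Evaluation section's survey paragraph accordingly, so that it agrees with the Abstract and Survey data sources. It would help to state in the Analysis section whether dose is counted per cycle or cumulatively.

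The cost is about one sentence of text and a few items on a short paper survey in any cycle that would otherwise have been skipped, with a small extra burden on nurses. The Study status section reports that data collection began in February 2015, so the change helps only cycles not yet completed. If any round has already been skipped, the report should state how many were held on each ward and which reports the dose value covers.

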##### Process measures

Process measures include self-reported uptake of feedback reports (survey data), intent to change behaviour (survey data) and perceptions of the feedback report (survey data on report content, presentation; interview data).

##### Outcome measures

Outcome measures include point-prevalence audit data and medication error reports. While we expect to observe an increase in medication error reporting rate as a result of the intervention, at some point, potentially as a culture of medication safety is developed, we may observe a decrease in medication error reporting because the true rate of errors decreases.

### Post-intervention data collection

Following the 12-month intervention period, the ACT will be administered to all nurses on all four wards. Six months following completion of the intervention phase (18 months post-baseline data collection), a repeat point-prevalence chart audit will be undertaken and a report of reported medication errors and AEs for the previous 6 months will be extracted from RiskMan. These data will be used to assess sustainability of the intervention. Fig. 1 illustrates the stages of the data collection.

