### Data sources

#### Audit data sources

Two sources of audit data will be used in the feedback report:Medication error reports and medication adverse event data that are routinely reported in the risk management and reporting system (RiskMan.Net ©) in the study organisation andData generated from point-prevalence audits of medication documentation in patients’ medical records.

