### Procedure

#### Baseline data collection

The Alberta Context Tool will be administered to all nurses on all four wards prior to implementation of the intervention. Point-prevalence audit data will be collected at baseline in all four wards, and a report of medication errors recorded for each ward for the previous 12 months will be extracted from RiskMan.

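### The RiskMan series is described with inconsistent content, and its extraction method changes at the interruption and again at follow-up, so an artificial step is possible; one end-of-study query would remove it

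*Protocol article*

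**What the plan says.** The article describes the RiskMan data in several places.

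- **Source** (Audit data sources): "Medication error reports and medication adverse event data that are routinely reported in the risk management and reporting system". This describes input to the feedback report and covers both errors and AEs.
- **Before** (Baseline data collection): "a report of medication errors recorded for each ward for the previous 12 months will be extracted from RiskMan". This is one retrospective report, and its wording names errors only.
- **During** (Evaluation): "routinely reported RiskMan data will be extracted weekly and point-prevalence chart audits will be conducted quarterly on all four wards". The same section gives the RiskMan content of the feedback reports as "medication-related errors and AEs (from RiskMan data) will be produced", so AEs are included.
- **After** (Post-intervention data collection): "a report of reported medication errors and AEs for the previous 6 months will be extracted from RiskMan". This is again one retrospective report, now naming errors and AEs.
- **After, in the abstract** (Methods/design): "a report of routinely collected medication errors for the previous 6 months is obtained". This is the same extract, with errors only.
- **Outcome** (Outcome measures): "Outcome measures include point-prevalence audit data and medication error reports". The Analysis section likewise names error report rates from RiskMan, aggregated by ward and analysed as an interrupted time series. Neither section says that AEs are part of the analysed count.

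**The concern.** An interrupted time series attributes a change in level or slope at a known date to what happened on that date. It therefore needs the outcome to be ascertained in the same way on both sides. Here the stated method moves from one retrospective report to weekly pulls at the interruption, and back to one retrospective report for follow-up. The content wording also differs between the baseline extract and the later ones.

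Two mechanisms could create a step without any change in reporting behaviour:

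- **Case definition.** If AEs are counted from the intervention onward but not at baseline, counts rise at the interruption.
- **Late entry.** A retrospective report includes incidents that were entered or reclassified late. A weekly pull indexed by event date and never refreshed does not. Counts would then fall at the interruption and recover at follow-up.

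Either could bias the estimated effect. Late entry could also distort the sustainability assessment.

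**Working it through.** The article gives no event counts, AE share, entry delay or power calculation for this series, so there is no stated figure to reproduce. All shares and losses below are assumptions.

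**1. Period lengths.** 12 + 12 + 6 = 30 months. The follow-up extract falls at 12 + 6 = 18 months after baseline, as the article says.

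**2. Extracts side by side.**

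| Period | Content as worded | Method |
|---|---|---|
| Before, 12 months | errors | one retrospective report |
| During, 12 months | errors and AEs (from the feedback-report content) | weekly pulls |
| After, 6 months | errors and AEs in the body text; errors in the abstract | one retrospective report |

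In the body text there are two content wordings and two extraction methods. Content changes once, at the interruption. Method changes twice.

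**3. Definition step.** Let *a* be the AE share of the combined count, with AEs counted only from the interruption onward and no true effect. The uncontrolled ratio is 1/(1 − *a*):

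- *a* = 5%: 1/0.95 = 1.05
- *a* = 10%: 1/0.90 = 1.11
- *a* = 20%: 1/0.80 = 1.25
- *a* = 30%: 1/0.70 = 1.43

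The controlled ratio is (1 − *a* in control)/(1 − *a* in intervention):

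- equal shares: 1.00
- 20% intervention, 10% control: 0.90/0.80 = 1.125
- 10% intervention, 20% control: 0.80/0.90 = 0.889

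On an additive scale equal shares are not enough. With *a* = 20% and assumed baseline rates of 3 and 1 reports per week, the shifts are 3/0.8 − 3 = 0.75 and 1/0.8 − 1 = 0.25, a spurious difference of 0.5 per week.

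Noise-free segmented regressions over 52, 52 and 26 weeks, Poisson for the ratios and linear for the additive case, gave these same controlled results. The step was identical in the intervention and follow-up phases, so content adds nothing new at the start of follow-up.

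**4. Late-entry step.** Let *m* be the proportion of reports that unrefreshed weekly pulls miss. The controlled ratio at the interruption is (1 − *m* in intervention)/(1 − *m* in control):

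- 5% intervention, 15% control: 0.95/0.85 = 1.12
- 15% intervention, 5% control: 0.85/0.95 = 0.89

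If the follow-up report is complete, counts then rise by 1/0.95 = 1.05 to 1/0.85 = 1.18 with no change in behaviour. In the first case the controlled ratio returns from 1.12 to 1.00, which would look like an effect that was not sustained.

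**5. Opposite signs.** With *a* = 10% and *m* = 10% in one arm, the interruption step is (1/0.90) × 0.90 = 1.00, but late entry still produces 1/0.90 = 1.11 at follow-up.

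**6. Scale.** The single-ward pilot reported an 80% increase. A definition step of that size would need 1/(1 − *a*) = 1.80, that is *a* = 1 − 1/1.80 = 44%.

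**The case against.** The strongest reply is that these are loose descriptions of one dataset. All the data come from one system, the abstract and the body name the same follow-up extract differently, and an extract is not an outcome numerator. The outcome is named as error reports, and the section on developing the intervention mentions error report rates and AE rates as separate items. AEs may therefore be extracted and never enter the count. The late-entry mechanism assumes pulls that are frozen and indexed by event date. The article fixes neither, and such rules are commonly left to a fuller document. The design is also controlled, and weekly extraction covers all four wards.

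Much of this stands. A reader might infer three different case definitions, or a definition-driven jump at follow-up. The text does not support either: weekly is a frequency, and the intervention-phase content already includes AEs. Nor can a reader conclude that follow-up lacks controls, because that section points to a figure that is not shown. Rate denominators may be left to the analysis plan, and no comparison of a 6-month with a 12-month total is specified, so seasonal confounding does not follow from the text.

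Two things remain. The extraction method does change, as written, at both boundaries. And the controls protect only if the arms are alike. The limitations section concedes that matched wards may differ. The intervention aims to improve the quality as well as the frequency of reporting, and the Background notes that harmless errors tend to go unreported, so the mix of errors and AEs could shift on intervention wards. Entry delay is not a stated target, so unequal delay is a possibility only.

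**Conclusion.** The concern is upheld in limited form. The RiskMan content is worded inconsistently between baseline and later extracts, and between the abstract and the body for follow-up. The stated extraction method changes at the interruption and changes back at follow-up.

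An artificial step at the interruption is possible if AEs are counted only after baseline or if weekly pulls are not refreshed. At follow-up only the late-entry route can act. Neither is shown to occur. Similar AE shares and entry delays in both arms would cancel the artefact on the ratio scale, but two wards per arm do not ensure that.

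The size is unknown. Under the assumed differences between arms it is about 11 to 12% in either direction, well below the pilot's 80%. The pilot was an uncontrolled before-after comparison on one ward, however, and the review evidence cited in the Background points to small improvements from audit with feedback. Against an effect of that order, an artefact of 12% would matter.

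**What to change.** 1. Reconcile the abstract and the sections on audit data sources, baseline collection, evaluation, outcome measures and post-intervention collection to one RiskMan case definition. It should match the stated outcome: medication error reports, with AEs counted separately.
2. For the analysis, re-extract all 30 months for all four wards in a single end-of-study query under that definition, with one date index throughout.
3. Keep the weekly pulls for the feedback reports only.

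With one definition in all periods the definition step is 1.00 by construction, and a single query removes the contrast between weekly and retrospective pulls. The cost is one extra database query and a few reworded sentences. It remains feasible after the start of data collection, because the plan already relies on retrospective RiskMan reports at baseline and follow-up.
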